#### Analysis plan

Patients will be analyzed in the groups to which they are assigned (intention-to-treat). Oncologic outcomes and OS will be calculated from date of randomization using the Kaplan-Meier method. A one-sided, one-sample binomial test will be used for the primary endpoint as described above. For actuarial comparisons between arms, the stratified log-rank test will be used (stratified by stratification factors). An two-sample T-test will be used to compare QoL scores at 1-year. The percentage of patients in each arm who experience a clinically significant QoL decline on the MDADI (10 points) will also be reported.

MBSImP™© scores will be compared at 1-year, including the total score, and the scores on the oral and pharyngeal subscales, using a two-sample T-test or a Wilcoxon rank sum test as appropriate. DIGEST™ and FOIS scores will be compared using the Chi-square test.

Pre-planned subgroup analysis will occur based on the stratification variables (nodal status [pN0 vs. pN+] and use of concurrent chemotherapy), as well as based on the neck dissection performed (unilateral vs. bilateral), and T-stage (T1–2 vs. T3–4). There will also be a pre-planned analysis based on the extent of nodes harvested in the pN0 neck (< 18 vs. 18 or more), depth of invasion of the primary tumour (< 4 mm vs. 4 mm or more), and photon versus proton treatment.

Multivariable Cox proportional hazards or logistic regression analysis, as appropriate, will be used to determine baseline and pathologic factors predictive of pN0 neck failure, DFS, OS, locoregional recurrence and salvage therapy. For the secondary endpoints involving QoL scales, linear mixed effects models will be used; for the MDADI, the total scores will be compared between the two arms, whereas for the EORTC QLQ-C30 and H&N35 scales, each of the subscales (e.g. pain, swallowing, etc.) will be compared between the two arms.

Rates of grade ≥ 2 toxicity and use of feeding tubes will be compared between arms using the Chi-square or Fisher’s exact test, as appropriate.

Utilities will be calculated from the EQ-5D-5L which will be administered at baseline and at 6 month intervals. Quality adjusted life years (QALYs) will be assessed as the area under the preference-weighted survival curve. Overall costs of each treatment strategy will be abstracted from the available literature. The incremental cost effectiveness ratios (ICERs) between treatment arms will be compared through the standard method of ratio between differences in costs and QALYs. Point estimates for these differences can be derived from multivariable generalized estimating equations (GEE) or generalized linear model (GLM) analyses.

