#### Measurement of outcomes

**pN0 neck failure:** measured as time from randomization until disease recurrence in the initially pN0 hemi-neck(s). Patients with prior or simultaneous recurrence at the primary site or in the initially pN+ hemi-neck will be censored for this outcome as of that timepoint. The primary endpoint is a comparison of pN0 neck failure in Arm 2 vs. historical controls; this endpoint will also be compared between the two arms as a secondary endpoint.**OS:** measured as time from randomization until death from any cause.**DFS:** measured as time from randomization to either recurrence at any location or death, whichever occurs first. New primary tumours will not count as DFS events.**Local recurrence:** measured as time from randomization until disease recurrence at the primary site.**Regional recurrence:** measured as time from randomization until disease recurrence anywhere in the neck.**Locoregional recurrence:** measured as time from randomization until disease recurrence anywhere in the neck or at the primary site, whichever occurs first.**Recurrence in the pN0 neck without other locoregional recurrence:** measured as time from randomization until disease recurrence in the pN0 neck alone without recurrence at the primary site or pN+ neck.**Rate of salvage surgery and/or radiation in pN0 neck:** measured as time from randomization to salvage intervention (surgery ± radiation) in the pN0 neck. Freedom from unsalvageable neck recurrence will be reported as the time from randomization to development of a neck recurrence in the pN0 neck that could not be salvaged.**Feeding Tube Insertion:** Rate of feeding tube insertion after start of radiation (either gastric, gastrojejeunal, or nasogastric) and rate of feeding tube use at 1-year post-randomization. Patients with feeding tubes inserted prior to randomization will be censored for this endpoint.**Rate of failure in the clinically node negative neck**: for patients who have unilateral neck dissections, the cN0 neck may be treated with radiation or observed, at the discretion of the treating oncologist (see section 6). This is measured as the time from randomization to failure in the cN0 neck, and will be reported for the whole group of patients who had unilateral dissections, and also stratified by whether radiation was delivered to that area.

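### Kaplan-Meier is specified for recurrence and salvage endpoints that do not count death as an event, so the absolute rates will overstate the proportion of patients with the event

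*Protocol article*

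**What the plan says.** The Analysis plan sets one estimator for all time-to-event outcomes: "Oncologic outcomes and OS will be calculated from date of randomization using the Kaplan-Meier method". It makes no exception for any recurrence endpoint. Arms are compared as follows: "For actuarial comparisons between arms, the stratified log-rank test will be used (stratified by stratification factors").

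The endpoints are defined under Measurement of outcomes. Apart from OS itself, death is an event only for DFS, "measured as time from randomization to either recurrence at any location or death, whichever occurs first". The others count their own event and nothing else:

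- Local recurrence is "measured as time from randomization until disease recurrence at the primary site".
- Regional recurrence is "measured as time from randomization until disease recurrence anywhere in the neck".
- Salvage is "measured as time from randomization to salvage intervention (surgery ± radiation) in the pN0 neck".
- Locoregional recurrence, isolated pN0-neck recurrence, unsalvageable neck recurrence and cN0-neck failure follow the same pattern.

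For pN0-neck failure a second kind of competing event is explicitly censored: "Patients with prior or simultaneous recurrence at the primary site or in the initially pN+ hemi-neck will be censored for this outcome".

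The primary test is a separate matter: "A one-sided, one-sample binomial test will be used for the primary endpoint as described above". The article names no cumulative-incidence or other competing-risk method.

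**The concern.** A patient who dies without recurrence can no longer recur. Kaplan-Meier treats that patient as censored, that is, as someone who would have gone on to recur at the same rate as those still at risk. One minus Kaplan-Meier then estimates the risk in a hypothetical population from which death has been removed, and does so only if the censoring is independent. It does not estimate the proportion of enrolled patients who recur.

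This is a stated choice of method that does not fit the stated endpoints, so it is not a detail left to an analysis plan that is not shown. It matters because the trial is framed around absolute risk. The Objectives and Sample size sections both treat a nodal recurrence risk of 15–20% as the level that warrants irradiating a nodal basin, and the Discussion says that the results will inform phase III trials. For salvage, the natural reading of a rate is the share of patients actually salvaged, which this estimator does not give.

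Deaths without a local or neck event are to be expected. The eligibility criteria admit ECOG 0–2, pT3–4 disease, positive nodes and ENE. Distant relapse is not an event for any local or neck endpoint, so deaths that follow it also compete.

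**Working it through.** **The plan's own figure.** The only related figure is the 83.1% power of the primary test. With 60 patients in Arm 2 and 5% dropout, 60 × 0.95 = 57 are evaluable. An exact one-sided binomial test of 80% control against 92%, which succeeds with at least 51 of 57 controlled (at most 6 failures), has attained alpha 0.0451 and power 0.8313. The stated figure reproduces, and no Kaplan-Meier estimate enters it.

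**Inputs for the check.** The protocol states no rate of death without recurrence, so a range is assumed: net risk of competing death d = 5%, 10%, 20% or 30% by 2 years. Net means the risk of dying that would apply if the event of interest could not occur. The Kaplan-Meier failure rates K = 15% and 20% are the two ends of the protocol's own threshold.

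**Formulas**, with constant and independent hazards over t = 2 years:

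- event hazard h1 = −ln(1 − K)/t
- competing death hazard h2 = −ln(1 − d)/t
- cumulative incidence = h1/(h1 + h2) × [1 − exp(−(h1 + h2)t)], where exp(−(h1 + h2)t) = (1 − K)(1 − d)

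**Worked case, K = 20% and d = 30%.** h1 = 0.2231/2 = 0.1116 and h2 = 0.3567/2 = 0.1783. The ratio h1/(h1 + h2) is 0.3849, and 1 − 0.80 × 0.70 = 0.44. Cumulative incidence = 0.3849 × 0.44 = 16.9%.

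**Results at 2 years**

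| Assumed d | Actual incidence if K = 15% | Excess (points) | Actual incidence if K = 20% | Excess (points) |
|---|---|---|---|---|
| 5% | 14.6% | 0.4 | 19.5% | 0.5 |
| 10% | 14.3% | 0.7 | 19.0% | 1.0 |
| 20% | 13.5% | 1.5 | 18.0% | 2.0 |
| 30% | 12.7% | 2.3 | 16.9% | 3.1 |

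The relative overstatement is about 2.5% at d = 5%, 11% at d = 20% and 18% at d = 30%.

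**Longer follow-up.** QoL assessments run to 60 months, so a 5-year illustration is relevant. With K = 30% and an assumed d = 40%, the ratio is 0.3567/(0.3567 + 0.5108) = 0.4112 and 1 − 0.70 × 0.60 = 0.58. The incidence is 0.4112 × 0.58 = 23.85%, an excess of 6.15 points.

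**Unequal deaths between arms.** Take K = 20% in both arms, with d = 20% in one and 30% in the other. Kaplan-Meier shows 20% in both. Cumulative incidence shows 18.0% and 16.9%. Under this model it is cumulative incidence, not Kaplan-Meier, that moves with mortality.

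**The case against.** Several points on the other side are sound.

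- **The target is not fixed.** The overstatement exists relative to the actual proportion of patients with the event. One minus Kaplan-Meier is a legitimate estimate of net risk under independence, and the article does not say which quantity it wants. This stands as a limit on the wording. It does not rescue rates that will be read as proportions of patients.
- **The effect may be small.** At 5–10% competing death the excess is at most 1 point at these rates. The standard error of a 15% rate is √(0.15 × 0.85/30) = 6.5 points in Arm 1 and √(0.15 × 0.85/60) = 4.6 points in Arm 2, against a largest excess of 2.3 points at that rate. This stands, although the error is systematic and always in one direction.
- **The direction is cautious.** Overstating failure in Arm 2 cannot make omission look safer in absolute terms. This also stands.
- **Salvage is partly inferred.** The article does not define which outcomes are oncologic, and its regression paragraph allows Cox or logistic models for salvage. Salvage is nevertheless defined as a time from randomization, so Kaplan-Meier is the plausible reading.

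Two stronger readings are tempting, and the documents support neither. A reader might infer that unequal deaths would distort the Kaplan-Meier comparison of the arms. The last calculation shows the reverse under independent hazards, and the planned stratified log-rank test is a valid cause-specific comparison. A reader might also infer that the primary decision is biased. It rests on a binomial test. How patients who die or are censored enter that test is a separate question.

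**Conclusion.** The point holds for the descriptive absolute rates of the secondary recurrence and salvage endpoints, and for any descriptive curve of pN0-neck failure. As written, deaths without the event can only be censored, so one minus Kaplan-Meier is never below the actual incidence, and exceeds it once a competing death precedes a later event.

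The direction is certain, but the size cannot be fixed from the documents. Over the assumed 5–30% competing death, the 2-year excess runs from 0.4 to 2.3 points at a Kaplan-Meier rate of 15% and from 0.5 to 3.1 points at 20%. These figures rest on constant, independent hazards. The upper end is material against a 15–20% decision band, and the lower end is minor. OS, DFS, the primary test and its power, and the stratified log-rank and Cox analyses are not affected. This is a correction to how secondary rates are reported and does not put the trial's main conclusion in doubt.

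**What to change.** In the Analysis plan, restrict Kaplan-Meier to OS and DFS. For local, regional, locoregional, isolated pN0-neck and cN0-neck recurrence, salvage and unsalvageable neck recurrence, report absolute rates by the Aalen-Johansen cumulative incidence function, with death before the event as a competing event. Do the same for the descriptive pN0-neck failure curve, and there also treat the other locoregional recurrence that is now censored as a competing event.

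Keep the stratified log-rank as the between-arm test and the Cox models as planned, both described as cause-specific. Gray's test may be added as a supplement. It should not replace the log-rank, because it would mix mortality into the treatment comparison.

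The change is to wording and should be made before results are seen. Deaths are already recorded for OS, so no new data are needed. The cost is slightly more analysis work, and each cumulative incidence must be read alongside mortality in the same arm.

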#### Pre-treatment evaluation

History and physical examination by a radiation oncologist within 5 weeks prior to randomizationStaging prior to randomization:
◦ CT or MRI of the neck (with contrast unless contraindicated) within 14 weeks of randomization. This can include the pre-operative CT, or the radiation therapy CT or MRI simulation if reviewed by a radiologist.
▪ In some instances, suspicious lymph nodes are visible on the scan after surgery. In such instances, recurrence must be ruled out pathologically before enrollment, either with a needle biopsy or resection of these nodes.◦ CT of the chest or whole body PET-CT (usually prior to surgery, must be within 14 weeks of randomization)Histological confirmation of SCCPregnancy test for women of child-bearing age within 2 weeks of randomizationDental evaluation prior to starting treatment, except edentulous patientsAssessment of dysphagia using NCI-CTC version 4.03 within 2 weeks of treatment initiationCompletion of QoL scoring prior to initiation of treatmentPrior to randomization, radiation contours are to be peer-reviewed and approvedMBS at baseline prior to initiation of treatment with documentation of the MBSIimP™©, DIGEST™ and the FOIS scores

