#### Statistical considerations

##### Sample size

The primary endpoint is the rate of relapse in the pN0 neck (i.e. the regional relapse rate in the pN0 neck) in Arm 2, compared to historical controls. All other endpoints are a comparison between Arm 1 and Arm 2.

It is generally accepted that a risk of nodal recurrence of 15–20% is sufficient to warrant radiation to a nodal basin, and therefore we wish to exclude a risk of regional recurrence in the pN0 neck of 20% at 2-years. Using a one-sided, one-sample binomial test, allowing for 5% dropout, a sample size in Arm 2 of 60 patients provides 83.1% power at a 0.05 significance level to detect a regional control rate in the pN0 neck of 92%, compared to an unacceptable level of 80%.

This sample size (30 in Arm 1 and 60 in Arm 2) also allows for > 80% power to detect a 10-point difference in the total MDADI score at 1 year (a secondary endpoint), assuming the scores are normally distributed with a standard deviation of 15 in each arm. It is generally believed that a 10-point difference in standardized QoL scores represents a clinically significant difference in QoL [42]. It is assumed that the QoL scores will be normally distributed with a standard deviation of 15 in each arm. The MDADI will be calculated as the composite score, but will also be reported for each of the subscales.

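### The 1-year QoL comparison, including the powered MDADI endpoint, uses an unadjusted t-test although baseline scores and stratification factors are available, and the plan does not say whether it or the mixed model governs month 12

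*Protocol article*

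**What the plan says.** All references are to the protocol article.

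- **Secondary endpoints** lists two QoL endpoints on the same instruments. One is QoL at 1 year. The other is QoL from treatment completion to 60 months, a schedule that includes month 12.
- **Sample size** powers one of these. The 30 and 60 patients are said to give "> 80% power to detect a 10-point difference" in total MDADI at 1 year, "assuming the scores are normally distributed with a standard deviation of 15 in each arm". The 5% dropout allowance is stated only in the primary-endpoint calculation.
- **Analysis plan** first says "An two-sample T-test will be used to compare QoL scores at 1-year" and names no covariates. Later in the same section: "For the secondary endpoints involving QoL scales, linear mixed effects models will be used", with total MDADI compared between arms. No time point, covariates or order of precedence is attached. The section also plans to report the share of patients with a 10-point MDADI decline. Time-to-event comparisons use a log-rank test stratified by the randomization factors. One-year MBSImP scores get a t-test or a rank-sum test.
- **Enrollment, randomization and allocation** stratifies by overall nodal status and concurrent chemotherapy.
- **Pre-treatment evaluation** calls for completion "of QoL scoring prior to initiation of" treatment, and the baseline modified barium swallow (MBS) has the same limit. The radiation contours, by contrast, must be peer-reviewed and approved before randomization.
- **Study design** describes the trial as open-label.

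**The concern.** Three things are at stake.

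1. **Precision.** Patients enter after different resections, so part of the 1-year MDADI variation was probably present at baseline. A t-test on the 1-year score leaves that variation in the error term and does not correct a chance baseline imbalance, which is a practical risk with 30 patients in one arm. It also ignores the stratification factors, although the log-rank comparisons use them.

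2. **Which result counts.** The mixed-model sentence, as worded, covers every secondary endpoint on a QoL scale, and QoL at 1 year is one of them. Month 12 can therefore be estimated in two ways. If the two disagree, the article gives no basis, fixed in advance, for choosing between them.

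3. **Baseline timing.** A self-reported baseline may be completed after the patient knows the allocated arm. That could influence the baseline value itself, and with it any baseline-adjusted analysis and the 10-point decline rate.

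**Working it through.** **Inputs from Sample size:** 30 and 60 patients, difference 10 points, SD 15.

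**Assumptions:** two-sided alpha of 0.05 (the article gives 0.05 for the primary test only, and no sidedness for MDADI); equal proportional loss in both arms; a correlation *r* between baseline and 1-year MDADI, which the article does not give, so a range is shown.

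**Step 1. Reproduce the stated power.**

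Standard error = 15 × √(1/30 + 1/60) = 15 × √0.05 = 3.354.

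Non-centrality = 10 / 3.354 = 2.981, with 88 degrees of freedom and critical *t* = 1.987.

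Power from the non-central *t* distribution = 83.9% (normal approximation 84.6%). The claim of more than 80% reproduces.

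**Step 2. Missing 1-year scores, unadjusted t-test.**

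| Missing | Patients | Non-centrality | Power |
|---|---|---|---|
| 0% | 30 / 60 | 2.981 | 83.9% |
| 5% | 28.5 / 57 | 2.906 | 81.9% |
| 10% | 27 / 54 | 2.828 | 79.8% |
| 20% | 24 / 48 | 2.667 | 74.9% |

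With whole patients, 28 / 57 gives 81.5% and 27 / 55 gives 80.0%. Power therefore first drops below 80% at about 10% missing. On the normal approximation the 10% case is still 80.7%, and the crossing is at about 12%.

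**Step 3. Adjust for baseline.** Replace the SD by 15 × √(1 − *r*²):

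- *r* = 0.3: 15 × √0.91 = 14.31
- *r* = 0.5: 15 × √0.75 = 12.99
- *r* = 0.7: 15 × √0.51 = 10.71

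| Missing | Unadjusted | *r* = 0.3 | *r* = 0.5 | *r* = 0.7 |
|---|---|---|---|---|
| 0% | 83.9% | 87.1% | 92.6% | 98.5% |
| 10% | 79.8% | 83.4% | 89.7% | 97.5% |
| 20% | 74.9% | 78.7% | 85.9% | 95.8% |

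Deducting three degrees of freedom, for baseline and the two strata, changes these figures by less than 0.1 percentage point.

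This is an ANCOVA approximation. A repeated-measures model was not computed, and no gain from the strata is credited.

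**Step 4. Read the two method sentences together.** Secondary endpoints has one 1-year and one longitudinal QoL endpoint, so the t-test may be meant for the first and the mixed model for the second. The mixed-model sentence is not limited to the longitudinal endpoint, and that endpoint itself includes month 12 on the same MDADI. Neither sentence gives precedence.

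**The case against.** The strongest reply is that nothing here is an error. An unadjusted t-test is valid in a randomized comparison, MDADI is a secondary endpoint of a phase II trial, and the power statement matches the named test. The two methods map naturally onto the two QoL endpoints. Mixed-model covariates and missing-data handling may be set out in a full protocol or SAP that is not shown.

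Much of that stands:

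- A reader might infer that the power claim is wrong, or that power fails as soon as any patient is missing. It does not. The claim holds with complete data and at the only dropout figure the article names, 5%.
- A reader might infer a flat contradiction between the two methods. With two QoL endpoints listed, it is an ambiguity.
- The gain depends on *r*. At *r* = 0.3 with 20% missing, the adjusted power of 78.7% is still below 80%.
- The article permits the baseline questionnaire after randomization but does not require that timing. Additional file 2, with the follow-up schedule, is not shown.
- For MBSImP, the text names only baseline and 1 year, so it gives no basis for a repeated-measures model there.

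One part does not stand. The 1-year test is stated in the article, not left to a later document. As stated, it passes over baseline scores that are collected anyway and strata that the log-rank comparisons do use.

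There may also seem to be a tension in asking for adjustment by a baseline whose timing is criticised. Completing the baseline before randomization removes it.

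**Conclusion.** The point holds as an avoidable loss of precision plus an unresolved choice of analysis; the plan's power figure is not wrong. The t-test has 83.9% power with complete data and about 80% until roughly 10% of 1-year scores are missing. Baseline adjustment would add 3.2 percentage points at *r* = 0.3 (87.1 − 83.9) and 8.7 at *r* = 0.5 (92.6 − 83.9) with complete data. With 10% missing it would add 3.6 (83.4 − 79.8) and 9.9 (89.7 − 79.8).

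These gains rest on the assumed correlation, a two-sided 5% level and equal loss in both arms. The direction does not depend on the exact value of *r*: with these patient numbers, any appreciable correlation helps.

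The baseline-timing point is real but smaller, because the article allows a baseline after allocation without prescribing it. A reader might infer that the baseline data are already compromised; the article does not show that.

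**What to change.** 1. In the Analysis plan, name one definitive analysis for the 1-year MDADI contrast, adjusted for baseline MDADI and the two stratification factors. It can be the mixed model already planned, with its 12-month arm contrast as the test, or an ANCOVA at 1 year. Keep the t-test as supportive.
2. State that the rest of the mixed model serves the longitudinal QoL endpoint.
3. For 1-year MBSImP, use ANCOVA with the baseline score and the two strata.
4. In Sample size, state the allowance for missing 1-year MDADI scores.
5. In Pre-treatment evaluation, require baseline QoL and the baseline MBS before randomization, as is already done for the contours.

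Items 1 to 4 cost wording only and need no more patients. Item 5 costs minor scheduling at sites, because the questionnaire and swallow study must fit in before allocation.

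### The 1-year QoL endpoint is assigned an unadjusted t-test that ignores earlier scores, and the mixed-model sentence also covers it without ranking the two; the planned model's month-12 contrast should be the main analysis

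*Protocol article*

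**What the plan says.** The Secondary endpoints section lists two QoL endpoints. One is QoL at 1 year on several scales, the MDADI first among them. The other is QoL over a series of visits up to 60 months, which again includes month 12.

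The Analysis plan first states "An two-sample T-test will be used to compare QoL scores at 1-year". Two paragraphs later it states "For the secondary endpoints involving QoL scales, linear mixed effects models will be used", and adds that total MDADI scores will be compared between arms. The second sentence is not limited to the endpoint over time.

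The Sample size section gives the power for the 1-year comparison of total MDADI scores: "This sample size (30 in Arm 1 and 60 in Arm 2) also allows for > 80% power to detect a 10-point difference". The assumption behind it is "It is assumed that the QoL scores will be normally distributed with a standard deviation of 15 in each arm". A dropout allowance appears only for the primary endpoint: "Using a one-sided, one-sample binomial test, allowing for 5% dropout, a sample size in Arm 2 of 60 patients".

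The Pre-treatment evaluation section requires QoL scoring before treatment starts, so a baseline score is planned for every patient.

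**The concern.** Total MDADI at 1 year is the only secondary endpoint with a stated power. Its analysis should be fixed in advance and should use the data well. Two features of the text work against that.

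- **Overlap.** The t-test sentence names 1-year QoL. The mixed-model sentence names all secondary endpoints on QoL scales, and 1-year QoL is one of them. The two methods can give different p-values on the same data, and in an open-label trial it is better that the choice between them is not left open.
- **Efficiency.** As described, the t-test uses only the month-12 scores. It makes no use of the pre-treatment score or of earlier visits, and a patient without a month-12 score contributes nothing. With 30 patients in the smaller arm, that lost precision matters.

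**Working it through.** **Inputs.** From the Sample size section: 30 and 60 patients, difference 10, SD 15. Assumed: two-sided 5%, since the section states no sidedness for the MDADI and its one-sided test belongs to the primary endpoint. Also assumed: the share of patients without a 1-year score (equal in both arms) and the correlation ρ between the pre-treatment and month-12 scores. The protocol gives neither.

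**Step 1: reproduce the stated power.** The standard error is SD × √(1/n₁ + 1/n₂) = 15 × √(1/30 + 1/60) = 3.354. The noncentrality is 10 / 3.354 = 2.981, with 88 degrees of freedom and critical value 1.987. The noncentral t distribution gives **83.9%** (normal approximation 84.6%). The claim of more than 80% reproduces.

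**Step 2: reduce both arms by the same share.**

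| Without a 1-year score | n₁, n₂ | Two-sided 5% | One-sided 5% |
|---|---|---|---|
| 0% | 30, 60 | 83.9% | 90.5% |
| 5% | 28.5, 57 | 81.9% | 89.2% |
| 9% | 27.3, 54.6 | 80.2% | 88.0% |
| 10% | 27, 54 | 79.8% | 87.7% |
| 15% | 25.5, 51 | 77.4% | 86.0% |
| 20% | 24, 48 | 74.9% | 84.0% |

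The two-sided t-test needs about 91% completion to stay above 80%. The normal approximation crosses 80% slightly later, between 11% and 12% missing.

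**Step 3: what the pre-treatment score adds.** Adjusting for a baseline score with correlation ρ reduces the residual SD to 15 × √(1 − ρ²). At 15% missing, with 25.5 and 51 patients and one degree of freedom spent on the covariate:

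- ρ = 0.4: SD 13.75, noncentrality 3.00, power 84.1%.
- ρ = 0.6: SD 12.00, noncentrality 3.44, power 92.4%.

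Simulation with about 15% missing at random agrees: 77–78% for the t-test, and about 85% (ρ = 0.4) to 93% (ρ = 0.6) for a regression on the pre-treatment score in patients with a month-12 score. Most of the gain therefore comes from the baseline score and not from the handling of missing forms.

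**Step 4: drop-out that depends on scores.** These simulations use an assumed mechanism and about 15% missing. When drop-out depends on the observed 6-month score, the t-test estimates about 9.1–9.5 points instead of 10, and a likelihood-based month-12 contrast estimates about 10.0. When drop-out depends on the month-12 state itself, the likelihood estimate is also biased (9.2–9.4, against 9.0 for the t-test).

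**The case against.** **The text has a natural reading without conflict.** There are two QoL endpoints and two methods. The t-test sentence names 1 year, and mixed models are the usual method for repeated scores. On the rule that the specific sentence governs the general one, the t-test serves the 1-year endpoint and the model serves the course over time. This is plausible and eases the conflict, although the protocol does not say so. It still leaves the less efficient test as the analysis of the only secondary endpoint with a stated power.

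**A reader might infer that the power statement is wrong.** The protocol does not support that. The figure is correct with 90 scores and at 5%, the only dropout rate the protocol gives. The 10% rate is an assumption, the shortfall there is 0.2 points, and it depends on an unstated two-sided test. At one-sided 5%, power is still 84.0% at 20% missing. The exclusion criteria also remove patients unable or unwilling to complete the questionnaires, which should limit missing forms.

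**A reader might infer that the t-test is biased and the mixed model is not.** That holds only under an assumed drop-out mechanism, as Step 4 shows. In these simulations the t-test's bias was about one point or less, towards no difference.

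**Missing-data handling may be in an analysis plan that is not shown.** That is so, and its absence from the article is not criticised here. The point rests on the two methods that the article does name.

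**Conclusion.** The point stands as an efficiency and clarity issue on a secondary endpoint. The protocol assigns 1-year QoL an unadjusted t-test, and its mixed-model sentence also takes in that endpoint without ranking the two. The primary endpoint is unaffected.

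The stated MDADI power is correct but has little reserve: it falls below 80% at about 10% missing and to 77.4% at 15%, if the test is two-sided at 5%.

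Using the pre-treatment score would bring power at 15% missing to roughly 84–93%. This rests on an assumed baseline correlation of 0.4 to 0.6; a weaker correlation would give a smaller gain. A likelihood-based model also remains valid when drop-out depends on scores already observed. It does not remove bias when drop-out depends on the unobserved month-12 state, for instance after a recurrence later than month 6.

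**What to change.** In the Analysis plan, name one main analysis of the 1-year QoL endpoint: the month-12 arm contrast from the planned linear mixed model. Specify visit as a factor, an arm-by-visit term, all available scores, and the two stratification factors as covariates. Label the two-sample t-test supportive.

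State how the pre-treatment score enters: as a covariate, or as an outcome with a common mean in both arms. This matters because a model that lets the arms differ freely at baseline gives up most of the precision gain. The Pre-treatment evaluation section asks only that the form be completed before treatment; for this use it should be completed before the allocation is known.

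Optionally, state in the Sample size section whether the MDADI test is one- or two-sided, and that more than 80% power for the unadjusted two-sided comparison needs a 1-year score from about 91% of patients.

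The cost is wording. The model is already planned and the scores are already collected; at most, the timing of the baseline form has to be confirmed.
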